## Abstract

**Background:**

Patients with pulmonary arterial hypertension (PAH) have reduced exercise capacity and poor quality of life. Exercise-based rehabilitation in PAH results in clinically relevant improvements in exercise capacity and hemodynamics. To clarify the mechanism, we will evaluate the effect of aerobic exercise training rehabilitation on right ventricular (RV) remodeling and function as determined measured by cardiac magnetic resonance imaging (CMR).

**Methods:**

We will conduct a 26-week multicenter randomized controlled trial. Patients on stable and unchanged PAH-targeted medication are randomly assigned (1:1) to the control and training groups. The primary endpoint is the RV stroke volume (RVSV) change from baseline to Week 26, determined by CMR. Comprehensive RV function is also performed using CMR. Other characteristics of the RV and left ventricle, World Health Organization functional class, 6-min walk distance, and N-terminal pro-B-type natriuretic peptide are included in secondary endpoints. We also investigate the proteomic, metabolomic, and transcriptomic changes after exercise training as exploratory endpoints.

**Ethics and Dissemination:**

The study and protocol were approved by the Ethics Committee of Shanghai Pulmonary Hospital (Approved No. of ethics committee: L20-17). The results will be disseminated at medical conferences and in journal publications. All participants will sign written informed consent.

**Trial Registration Number:**

ChiCTR2000031650.

## Introduction

Pulmonary arterial hypertension (PAH) is characterized by progressive remodeling of the pulmonary vasculature, which results in limited exercise capacity, progressive increase in breathlessness and right ventricular remodeling, and eventual death (1). Advances in PAH-targeted medications have significantly improved prognosis, and other therapies need to be further explored in order to improve exercise capacity and quality of life (QoL) (2). There is strong evidence that exercise training improves cardiorespiratory fitness, functional status, and clinical outcomes of patients with other heart or lung diseases (3, 4). There was a time when PAH patients were actively discouraged from exercise rehabilitation because of fear of exercise risk. However, exercise training has recently shown beneficial effects as add-on to PAH-targeted treatment in different etiologies of pulmonary hypertension (PH), such as IPAH (3, 5–8), inoperable chronic thromboembolic PH (CTEPH) (4), and associated PAH in connective tissue diseases (9).

Supervised rehabilitation, including exercise training have been proved to improve pulmonary hemodynamics, exercise capacity, QoL, and possibly RV function in patients with PH (Class I, A) (5–15). Currently, most exercise training trials published have focused on exercise capacity of patients with PH. The European Respiratory Society statement on exercise training and rehabilitation acknowledges that gaps in knowledge exist (15). Among them, the mechanisms of improved exercise capacity and hemodynamics by exercise training in PAH remain incompletely understood.

Increased cardiac output may be explained by a decreased RV afterload and direct training effect on heart. Therefore, further research on the effects of exercise training in PAH should consider the endpoints of RV properties.

Cardiac magnetic resonance imaging (CMR) is the gold standard for non-invasive assessment of RV function. Images of slices in any plane can be obtained with a very good spatial and temporal resolution. This translates into a low variability of inter-study and inter-rater CMR assessments which allows a reduced sample size for clinical trials compared to other imaging tools (16).

Therefore, a randomized controlled trial (RCT) comparing aerobic exercise training as an adjunctive therapeutic strategy is being conducted in China. This study aims to evaluate the effect of aerobic exercise training on right ventricular properties assessed by CMR in patients with PAH.

## Methods And Analysis

### Study Design and Setting

The study of the efficacy and safety of aerobic exercise training in PAH (the Saturday study) will recruit subjects from 1 June 2020 to 1 June 2023. The study is a 26-week multicenter, prospective, and RCT. Subjects willing to consider enrollment will be consented. Patients with PAH stable on PAH-targeted drugs for at least 3 months prior to inclusion are randomly assigned to the control and training groups. Medication remains unchanged during the study period (Figure 1). We will use the SPIRIT checklist and TIDiER checklist when writing our report (Supplementary Materials 1, 2) (17, 18). All centers will follow a standardized protocol, including rehabilitation, diagnosis, and evaluation of PAH, as shown in Table 1.

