### Rehabilitation Program With Aerobic Exercise Training

Exercise training is started in-the hospital for 2 weeks. Patients spend 30 min per session 3 days/week. A cardiopulmonary exercise test prior to enrolment was performed to determine the anaerobic threshold (AT). We perform interval cycle ergometer training at workloads of 1 min before the AT. The training intensity was adjusted by oxygen saturation (SaO_2_), heart rate (HR), and blood pressure monitored throughout the training. Patient receive oxygen supply throughout the training when SaO_2_ falls below 90% during exercise. Patients who were on daily oxygen before enrollment remain on oxygen. The exercise training includes two aerobic exercise training sessions, namely, 2-week supervised exercise training in the hospital and 10-week training at home. The home-based program is walking with exercise intensity at an AT of 30 min/day for 3 days a week for 10 weeks. Detailed FITT principle is shown in Table 1. In our study protocol, we choose AT intensity because AT intensity stands for aerobic exercise, which can avoid the accumulation of lactic acid in the body, avoid excessive activation of sympathetic nerve, excessive myocardial oxygen consumption, or arrhythmia. The AT intensity is expressed by the HR or the number of steps (the speed of the AT divided by the step distance). Patients in this group at home are managed by the *Xinankang* home electrical equipment system together with PAH experts, physiatrists, and physiotherapists. The home system consists of the portable electrical equipment and *the Xinankang* app for patients to upload their health data, and communicate with the *Xinankang* app uploaded by physiatrists and physiotherapists. This app also reminds participants to complete their training and follow-up on time (Figure 2).

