**Figure 2 F2:**
[figure not shown]
The screenshot for the portable electrical equipment and the *Xinankang* app for patients (English version). Instructions on how to wear a close-fitting the portable electrical equipment and rehabilitation record details including metabolic equivalent, heart rate and exercise prescription, etc.

Rehabilitation physicians review patients' health data during home exercise training, and provide suggestions. If the patient's condition worsens, the system can be used to coordinate a referral to the hospital. We applied the *Xinankang* app to integrate patients, home electrical equipment, and doctors. Adherence is assessed during telephone calls and review of the participant's exercise diary.

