### Adverse Events

Participants may voluntarily withdraw at any time, or if they experience a serious adverse event (SAE) that is associated with exercise training. All SAEs are discussed with the principal investigator who assesses seriousness and causality. Other adverse events (AEs), defined as any unfavorable and unintended sign, symptom or diseases, are also recorded. AEs are followed up until normalization, recovery or symptoms stabilize.

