### Statistical Analysis

Data will be presented as mean (SD), median (interquartile range), and frequency (percentage) available for data characteristics. For comparisons between groups, a *t*-test or rank-sum test will be applied for quantitative variables, while the χ^2^ test or Fisher's exact test for qualitative variables.

Primary and secondary endpoints will be analyzed using the whole population. However, patients who withdrew their consent, patients with severe protocol violations, or patients without the primary endpoint data, will be excluded from the whole population (26). An intention-to-treat analysis will be used to avoid, with inclusion of all available measures, regardless of whether participants completed the intervention, while the safety analysis will be done in the safety analysis population. Primary outcome analysis will be performed by an analysis of covariance (ANCOVA) model. Changes from baseline in RVSV will be analyzed using an ANCOVA with a factor for other PAH-specific therapies (none, background, or initiated at baseline) and a covariate for baseline RVSV. Missing outcomes were imputed as the multiple imputation. For analysis of categorical data, the McNemar–Bowden test will be used. *P* < 0.05 with two-sided test is considered statistically significant. All analyses will be performed with IBM SPSS V20 (IBM Corp., Armonk, NY, USA).

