## Discussion

Evidences suggests that supervised individually adjusted exercise training rehabilitation are likely to be safe for patients with PAH who are stable on PAH-targeted therapy (10, 13, 14).

Most exercise training trials published thus far have focused on exercise capacity of PH patients. There was only one study which assessed invasively measured hemodynamics changes at rest and during exercise as secondary endpoints (27). The study revealed a significant increase in the cardiac index at rest and exercise, decreases in the pulmonary arterial pressure and pulmonary vascular resistance at rest. Recent data suggest that the cardiac index during exercise may independently predict the survival of PAH patients (28). Improved RV function and hemodynamics by supervised exercise training may contribute to improved exercise capacity and QoL. Because invasive data are only available from a single perspective randomized study (27), further investigations are needed to confirm these data. Our study is the first to focus on aerobic exercise training for PAH patients in China. This prospective, randomized, controlled trial study will shed light on right ventricular properties.

In addition to assessing the efficacy of the intervention described above, this study will have several strengths. CMR-derived right ventricular remodeling parameters, RVEDV, RVESV, and RV mass, have independent prognostic value for all-cause death and composite end points of patients with PAH (25). In this study, we will first consider the RV remodeling parameters as endpoints. A combined effect on different molecular pathways and organs is likely to be the pathophysiological underpinning of the improvement associated with exercise training in PH (15). We will also investigate the proteomic, metabolomic, and transcriptomic changes after exercise training as exploratory endpoints. There were apparent changes or improvements made in patients where medication could have been adjusted but was not adjusted due to the ongoing study. This maybe the limitation of our study.

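### The primary analysis set is defined in two incompatible ways: exclusions after randomization against intention-to-treat with multiple imputation

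*Protocol article*

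**What the plan says.** All references are to the protocol article.

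- **Primary Efficacy Outcome:** the endpoint is the change in RVSV by CMR between baseline and Week 26.
- **Statistical Analysis, exclusions:** primary and secondary endpoints use what the paragraph calls the whole population, but "patients who withdrew their consent, patients with severe protocol violations, or patients without the primary endpoint data, will be excluded from the whole population".
- **Statistical Analysis, intention-to-treat:** the next sentence announces an intention-to-treat analysis "with inclusion of all available measures, regardless of whether participants completed the intervention".
- **Statistical Analysis, missing data:** "Missing outcomes were imputed as the multiple imputation".
- **Study Design and Setting:** "Medication remains unchanged during the study period". The article states no exception.
- **Discussion:** "There were apparent changes or improvements made in patients where medication could have been adjusted but was not adjusted due to the ongoing study". This is offered as a possible limitation.
- **Adverse Events:** "Participants may voluntarily withdraw at any time, or if they experience a serious adverse event (SAE) that is associated with exercise training".
- **Rehabilitation Program (text after Figure 2):** if the patient's "condition worsens, the system can be used to coordinate a referral to the hospital". The system is described for the training arm: "Patients in this group at home are managed by the" home equipment and app, together with the clinical team.
- **Sample Size Calculation:** 77 per group (154 in total), raised to 96 per group (192 in total) for 20% dropout.

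**The concern.** The primary analysis needs one rule for who is in it. The article gives two, a few lines apart. One removes patients for things that happen after randomization: withdrawal, a severe violation, or no Week 26 scan. The other keeps everyone as randomized and fills in what is missing. An analyst could follow either and claim to have followed the plan.

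The choice matters because the exclusions need not be independent of the outcome. PAH is progressive, and a patient who deteriorates is more likely to miss the Week 26 CMR, to withdraw, or to need a drug change. Deterioration is also plausibly tied to RVSV. A set selected in this way no longer has the protection of randomization. Patients know their allocation, and the article describes app monitoring and hospital referral only for the training arm, so the two arms need not lose such patients at the same rate.

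**Working it through.** **1. The plan's own figures.** 154 / 0.8 = 192.5, against 192 stated; in reverse, 192 × 0.8 = 153.6, or about 154. So 154 is the number that the plan itself expects to have left after dropout. The 77 per group comes out of the normal-approximation formula n = 2(1.96 + 1.28)² SD² / δ² only for selected inputs: δ = 10 and SD = 19 give 76 (77 with the t distribution), while δ = 9 with SD 18 to 22 gives 85 to 126. That is a separate matter, and nothing below depends on it.

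**2. Each type of patient under each rule.**

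| Patient | Exclusion sentence | Intention-to-treat and imputation sentences |
|---|---|---|
| No Week 26 RVSV | out | in, value imputed |
| Severe violation, Week 26 RVSV measured | out | in, value as measured |
| Consent withdrawn | out | in, with data collected before withdrawal |

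The first row is the direct contradiction: if every patient without Week 26 RVSV is out, the imputation sentence has nothing to act on for the primary endpoint. The second row contradicts the intention-to-treat label, because these patients have a measured outcome and are removed for conduct after randomization.

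**3. Size of the discrepancy.** Assume that all planned loss falls in the excluded categories, equally in both arms.

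- Exclusion reading: 77 × 2 = 154.
- Intention-to-treat reading: 96 × 2 = 192.
- Gap: 192 − 154 = 38 patients, that is 96 − 77 = 19 per arm, and 19 / 96 = 19.8%.

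This is the dropout allowance seen from two sides. It does not estimate how many patients would be lost through worsening. Violators with a measured RVSV would add to it, and a lower dropout rate would shrink it.

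**4. How exclusion can follow the outcome.** Withdrawal and a missed Week 26 scan lead to exclusion directly from the text. A drug change does so only if it is classed as a severe violation. The article does not define that term, and unchanged medication is one of its rules, so the text leaves this open.

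**5. What the bias would depend on.** Let p be the share of an arm that is dropped for worsening, and d the gap in mean RVSV change between retained and dropped patients, taken as equal in both arms. Dropping them raises an arm's mean by d × p, so the training-minus-control difference shifts by d × (pT − pC). It is zero if the shares are equal, understates benefit if more controls are dropped, and overstates it if more training patients are dropped. The document gives neither p nor d.

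For scale only, with assumed inputs d = 9 to 18 mL and shares 5 to 10 percentage points apart: 9 × 0.05 = 0.45 mL up to 18 × 0.10 = 1.8 mL. The standard error of the difference at 77 per arm is SD × √(2/77), or 2.9 to 3.5 mL for SD 18 to 22. The assumed shift is thus 0.45 / 3.5 = 0.13 to 1.8 / 2.9 = 0.62 standard errors.

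**The case against.** **The sentences might be reconciled.** Imputation could be meant for secondary outcomes in patients who do have RVSV, and including all available measures could mean an available-case analysis. The intention-to-treat sentence has also lost words, so part of the conflict may be poor drafting. This softens the imputation conflict. It does not rescue the violator exclusion, which removes patients whose outcome is available. It would also leave the primary analysis a complete-case analysis under an intention-to-treat label.

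**Imputation may change little.** If RVSV is imputed only from the baseline variables in the ANCOVA, the result is close to the complete-case answer. This stands, and it is why the fix asks for measures taken after baseline to inform the imputation.

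**A stronger reading is tempting.** A reader might infer that fixing medication for 26 weeks is itself an error, that worsening patients are denied treatment, and that those who receive it are dropped. The documents do not support this:

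- Fixed background therapy is a normal choice in a trial that asks about mechanism.
- A rescue rule may sit in the full protocol or in Figure 1, neither of which is shown. Its absence from an article is not a finding.
- No sentence classes a drug change as a severe violation or as a reason for withdrawal.
- The Discussion remark speaks of changes or improvements, and names neither worsening nor an arm.

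**The difference between arms is only a possibility.** The app is described for 10 weeks of home training within a 26-week study. Table 2 lists telephone contact, adverse-event monitoring and an early-termination visit without separating the arms.

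**Conclusion.** The point holds for the analysis set. As written, the Statistical Analysis section gives two different primary populations: 154 or 192 patients at the planned 20% loss, if all of that loss falls under the exclusions. Following the exclusion wording would produce a set chosen after randomization and possibly related to the outcome. That can bias the comparison, but the document supports no statement of size or direction, and the millilitre figures above rest wholly on assumed inputs. The fixed-medication rule is one example of how a worsening patient might come to be excluded, conditional on how a drug change is classed. It is not an error in its own right. The wording should be corrected before the data are analysed.

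**What to change.** In Statistical Analysis:

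- Delete the exclusions for missing primary endpoint data and for severe protocol violations from the primary analysis.
- Analyse all randomized patients in their assigned arm. For those who withdraw consent, use data collected up to withdrawal.
- Multiply impute missing Week 26 RVSV separately by arm, from baseline RVSV and other collected measures. Table 2 already lists 6MWD, WHO functional class, echocardiography and CPET at the early-termination visit, which is where informative values for such patients would come from.
- State that patients whose PAH therapy changes stay in follow-up and in the primary analysis, and report such changes by arm from the concomitant-medication data in Table 2.
- Move the exclusion of severe violators to a per-protocol sensitivity analysis.

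The cost is amended wording, an imputation model and one sensitivity analysis. The sample size need not change. The downside is that some Week 26 values will reflect added therapy, which would dilute a training benefit if controls are escalated more often. The sensitivity analysis and the counts by arm would let a reader judge this.

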**Figure 1 F1:**
[figure not shown]
Flow diagram of study recruitment and randomization.

**Table 1 T1:** Frequency, intensity, time, and type of exercise training.

	**In-hospital**	**Home**
Frequency	3 days per week for 2 weeks	3 days per week for 10 weeks
Intensity	in AT heart rate	in AT heart rate
Time	30 min/section	30 min/section
Type	Walking, cycling	walking, cycling

*AT, anaerobic threshold*.

### Eligibility Criteria

#### Inclusion Criteria

(a) Group 1 PAH (idiopathic, heritable, drugs, connective tissue diseases, or all kinds of congenital heart diseases) based on the diagnostic criteria of the 6th World Symposium on Pulmonary Hypertension (19); (b) age ≥ 18 or <60 years, (c) World Health Organization functional class (WHO FC) II or III, (d) stable and compensated under PAH-targeted medications, diuretics, and supplemental oxygen for at least 3 months; (e) willing to sign written informed after full explanation of this study; (f) 6-min walking distance (6 MWD) ≥ 200 m.

#### Exclusion Criteria

(a) Group 2–5 PH groups in accordance with diagnostic criteria (19).

(b) Uncontrolled hypertension (systolic blood pressure > 180 mm Hg or diastolic blood pressure > 110 mm Hg), unstable arrhythmias, angina or myocardial infarction, stroke or transient ischemic attach (within 3 months) (20).

(c) Inability to mobilize independently.

(d) Pulmonary embolism or deep vein thrombosis in the last 6 months prior to screening or without regular or standard anticoagulation.

(e) Neuromuscular disorders limiting rehabilitation.

(f) Unsuitable for participation by researchers, such as unsafe in exercise training or poor compliance.

### Recruitment and Consent

The potentially eligible subjects were provided informed consent documents for a comprehensive explanation of the trial. Participants will be identified by the clinical or rehabilitation physician, *via* screening strategies from the databases of our own PAH patients. As a general rule, patients with definitive diagnosis of Group 1 PAH who are willing to consider enrolment will be asked to provide consent.

### Rehabilitation Program With Aerobic Exercise Training

Exercise training is started in-the hospital for 2 weeks. Patients spend 30 min per session 3 days/week. A cardiopulmonary exercise test prior to enrolment was performed to determine the anaerobic threshold (AT). We perform interval cycle ergometer training at workloads of 1 min before the AT. The training intensity was adjusted by oxygen saturation (SaO_2_), heart rate (HR), and blood pressure monitored throughout the training. Patient receive oxygen supply throughout the training when SaO_2_ falls below 90% during exercise. Patients who were on daily oxygen before enrollment remain on oxygen. The exercise training includes two aerobic exercise training sessions, namely, 2-week supervised exercise training in the hospital and 10-week training at home. The home-based program is walking with exercise intensity at an AT of 30 min/day for 3 days a week for 10 weeks. Detailed FITT principle is shown in Table 1. In our study protocol, we choose AT intensity because AT intensity stands for aerobic exercise, which can avoid the accumulation of lactic acid in the body, avoid excessive activation of sympathetic nerve, excessive myocardial oxygen consumption, or arrhythmia. The AT intensity is expressed by the HR or the number of steps (the speed of the AT divided by the step distance). Patients in this group at home are managed by the *Xinankang* home electrical equipment system together with PAH experts, physiatrists, and physiotherapists. The home system consists of the portable electrical equipment and *the Xinankang* app for patients to upload their health data, and communicate with the *Xinankang* app uploaded by physiatrists and physiotherapists. This app also reminds participants to complete their training and follow-up on time (Figure 2).

